### Statistical analysis

#### Sample size

Sample size calculation was carried out based on expected effects regarding the primary outcome (physical function measured by the Short Physical Performance Battery [13] after 6 months of intervention (T1). A change of 1 point has been shown to be clinically relevant (e.g. predictive of future hospitalisation, health improvement and mortality) [33]. The standard deviation in comparable samples has ranged between 2.6 and 2.8 points [30, 31]. With a conservative approach, we assumed the higher standard deviation (2.8) for our calculation. In an analysis of covariance (including baseline values of the primary outcome), with an R-square of 0.5 for the covariate and a power of 95% (1-β), sample sizes of *n*=103 will be required for each of the two groups. The total sample of 206 participants achieves 95% power to detect differences among the means using an F test with a 5% significance level. The size of the variation in the means is represented by their standard deviation, which is 0.50. The common standard deviation within a group is assumed to be 2.8.

In our pilot study [12] conducted in nursing homes, we experienced a loss of 28% during the 6 months intervention period mainly due to death and hospitalisation. From our experience, the loss of participants recruited in primary care practices will be lower. A British primary care and community based study, which examined a complex nurse-delivered intervention with self-paced exercises and therefore people who are likely to be physically healthier (compared to our participants), experienced a loss of 6% during 3 months [9]. Considering that we are now also recruiting participants in community settings (living at home, primary care) and following a conservative approach, we set the expected loss during the intervention period to 40% (mainly due to death and hospitalisation). Assuming a loss of 40% during the 6 months of intervention we will need a total sample of *n*=345 to achieve adequate power of 95% at our primary endpoint. This will also enable us to achieve enough power for the analyses of secondary endpoints. The study centre Marburg will aim to recruit 230 persons from the community setting and the study centre Witten 115 from nursing homes.

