#### Data analysis

At T1, we will apply an analysis of covariance of the primary outcome physical function (SPPB scores). This outcome will be used to analyse the difference between the intervention and control group. In case of non-normally distributed data, we will apply a nonparametric covariance model [34]. The secondary outcomes will be evaluated with ANCOVAs, t-tests or distribution independent Mann-Whitney U-Tests. To compare the number of deaths, events leading to discontinuation of the intervention, falls requiring medical attention, and hospital treatments, we will either calculate a χ2-test, Fisher exact test for binary variables or conduct a log-rank-test. Since the number of falls or falling in general has shown to depend on fear of falling and the amount of physical activity, we will perform a mediator analysis to correctly identify the effect of our intervention on falling [35].

Furthermore, we will perform exploratory analyses (multifactorial ANCOVAs and in case of non-normally distributed data adjusted rank transform tests [36]) and dichotomise and evaluate whether the participants in the subgroups setting (community setting, nursing home), sex, rural/urban setting, frailty, and baseline SPPB score show different results in our primary outcome SPPB or in secondary outcomes. We will perform this analysis at T1 and T2.

The evaluation of the intervention will be performed as intention-to-treat (ITT). The ITT analysis will include all randomised participants irrespective of the actual performance of the intervention. In case a participant decides to withdraw consent, we will ask for a final evaluation.

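### Minor: splitting baseline SPPB and frailty in two for the exploratory effect-modification analyses costs roughly 23–36% of the information at a central cut if modification is about linear; the ordered scores could be used instead

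*Protocol article*

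**What the plan says.** The Data analysis section introduces these analyses as exploratory: "Furthermore, we will perform exploratory analyses (multifactorial ANCOVAs", with adjusted rank transform tests if the data are not normal. It then says the team will "dichotomise and evaluate whether the participants in the subgroups setting (community setting, nursing home), sex, rural/urban setting, frailty, and baseline SPPB score" differ in the primary or secondary outcomes, and adds: "We will perform this analysis at T1 and T2".

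Under Eligibility, SPPB must be below 9 at entry, and scores of 2 or less (nursing homes) or 3 or less (community) are excluded. Baseline SPPB therefore runs from 3 to 8 in nursing homes and from 4 to 8 in the community. Frailty is measured with the Clinical Frailty Scale; the article gives no categories or distribution for it.

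The Sample size section already uses the ungrouped baseline score: "In an analysis of covariance (including baseline values of the primary outcome), with an R-square of 0.5 for the covariate". The article gives no reason for splitting and no power figure for the subgroup analyses.

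**The concern.** Setting, sex and rural/urban location have two levels by nature. For them the instruction to dichotomise changes nothing. For baseline SPPB and frailty it replaces an ordered score by a high/low label. People at opposite ends of the same half are then treated as alike, and people one point apart across the cut as different.

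Eligibility has already narrowed SPPB to five or six values, so a split removes much of the remaining gradation. A treatment-by-score term needs no new data, because baseline SPPB and frailty are both measured at T0 and multifactorial ANCOVAs are already planned.

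At stake is the precision of an exploratory answer to whether the effect varies with starting function or frailty. Interaction tests are weak at this sample size, and a two-group contrast weakens them further when the trend is gradual. It also cannot show how the effect changes along the scale.

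**Working it through.** **1. The plan's own figure.** Inputs from the Sample size section: a 1-point difference ("A change of 1 point has been shown to be clinically relevant"), which equals a standard deviation of 0.50 between two means; within-group SD 2.8; R-square 0.5; two-sided 5%; power 95%.

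- Residual SD = 2.8 × √(1 − 0.5) = 1.98.
- Normal approximation: n = 2 × (1.960 + 1.645)² × 1.98² / 1² ≈ 102 per group.
- Noncentral F with one covariate: power 0.948 at 102 and 0.950 at 103 per group.
- 206 / (1 − 0.40) = 343.3, so 344 against the stated 345.

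The sample size reproduces, and the point does not touch it.

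**2. Information kept by a split.** With randomised treatment and a linear modifying effect, the share of interaction information kept equals the squared correlation between the score and its split:

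kept = q(1 − q)(m₁ − m₀)² / Var(score),

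where q is the share above the cut and m₁, m₀ are the mean scores above and below it. All score distributions here are assumptions.

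- Even over 3–8, cut at 6 or more: q = 0.5, means 7 and 4, variance 2.917. Kept = 0.25 × 9 / 2.917 = 0.771, **loss 23%**. Adjacent cuts lose 31%, end cuts 57%.
- Even over 4–8, cut at 6 or more: q = 0.6, means 7 and 4.5, variance 2. Kept = 0.24 × 6.25 / 2 = 0.750, **loss 25%**. End cuts lose 50%.
- Planned mix of 230 community and 115 nursing home, even within setting: best cut loses 25%, other cuts 29–80%.
- Bell-shaped over 3–8 (means 5.5 to 7, SD 1 to 1.5): best cut loses 28–31%.
- Normal score, median split: kept = 2/π = 0.637, **loss 36%**; a 30/70 split loses 42% and a 20/80 split 51%.
- Two-peaked over 3–8 (weights 3, 1, 1, 1, 1, 3): best cut loses **15%**.
- Frailty, on assumed categories 3–7 or 4–7: best cut loses 20–37%.

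**3. Effect on power.** If the test on the score has 80% power, power after the split = Φ((1.96 + 0.84) × √kept − 1.96):

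- kept 0.77: 69%
- kept 0.75: 68%
- kept 0.64: 61%

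**4. The trial's own scale.** Take 206 analysed, 1:1 allocation, an even split and residual SD 1.98. The standard error of the difference in effect between halves is √(4 × 3.92 / 206 × 4) = 0.552, where 3.92 = 1.98².

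- A 1-point difference in effect between halves: z = 1/0.552 = 1.81, power Φ(1.81 − 1.96) = 44%.
- The same linear trend tested on the score: z = 1.81/√0.771 = 2.06 to 1.81/√0.637 = 2.27, power 54–62%.
- With all 345 analysed, the figures are 65% against 76–84%.
- The smallest difference between halves with 80% power at 206 is 2.80 × 0.552 ≈ 1.55 points.

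**The case against.** The best counter-argument is that a split has some merit. A two-group contrast needs no linearity assumption, so if benefit sat beyond a threshold or peaked mid-range, a straight-line interaction could lose power or mislead. Groups also suit the planned rank-based fallback, which works with factors. That route may well be used, since the Missing data section assigns SPPB 0 after death or admission and 40% loss is expected, mainly for such reasons. This stands: the loss figures hold only for roughly linear modification, and the fix must cover the fallback.

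The wording is also loose. It could mean models plus a separate subgroup comparison, which would not rule out an ungrouped score in the models. That is possible, but the text attaches dichotomising to the named factors and mentions no interaction with an ungrouped score.

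A reader might infer three stronger things that the article does not support:

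- **That at least a quarter of the information is always lost.** Evenly spread scores over 3–8 give 23%, and two-peaked scores about 15%.
- **That splitting brings no benefit at all.** It is easy to display and free of a linearity assumption. The article simply claims neither.
- **That the absent cut-point is a defect.** It may be in a fuller protocol or analysis plan that is not shown.

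Finally, the Aims section poses no effect-modification question, so the weight of this analysis should not be overstated.

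**Conclusion.** The point holds as a cheap, minor improvement. Dichotomising is a stated choice rather than an omission, and it affects baseline SPPB and frailty only. At a central cut the cost is about 23–36% of the information for that interaction test, with about 15% possible for two-peaked SPPB scores, 20% for some assumed frailty categories, and more than 36% at off-centre cuts. This rests on three assumptions that the article neither gives nor excludes: the score distribution, the position of the cut and roughly linear modification.

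It would be wrong to infer any threat to the trial's main result. These analyses are labelled exploratory; the primary comparison, its type I error and the planned 345 participants are unaffected.

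**What to change.** In the exploratory ANCOVAs, test treatment-by-score interactions with baseline SPPB and the Clinical Frailty Scale as continuous or ordinal terms. Check for non-linearity, for example by adding a curved term or by comparing with a model that uses the separate score levels. Report the estimated treatment effect with its confidence interval across the score range. Keep binary factors for setting, sex and rural/urban, and use a high/low split of SPPB or frailty for display only. Where the rank-based fallback needs factors, enter ordered levels rather than two groups.

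The cost is a change to the analysis wording, a linearity assumption that has to be checked, and slightly more analysis work. Data collection, visits and sample size do not change.

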#### Missing data

If the T1 or T2 evaluation of a participant cannot be performed, the research assistant will decide whether an informative (death, admission) or non-informative event (e.g. moving to another municipality) has caused the evaluation to be missed. Information on reasons for missing the T1 or T2 evaluation will be obtained from participants’ families, general practitioners or nursing teams.

Depending on this categorisation, the following methods for analysis taking into account missing values will be used: 1) informative missing: not able to attend [examination] because of previous nursing home admission, hospital admission or death - tied worst rank score method will be assigned a SPPB Score = 0. For secondary outcomes, we will proceed in a similar fashion. In the analysis, we will apply the worst-rank score analysis [37]. It considers only the relative ordering of the values and applies the minimum variance linear or best linear estimator. For secondary outcomes, we will proceed in a similar fashion. 2) In case of non-informative missing (not able to attend because participant moved to another place without one of the conditions mentioned above), we will proceed with multiple imputation. In case of non-normally distributed data, we apply a nearest neighbour multiple imputation approach to estimate the proportion of each then categorised variable [38]. For secondary outcomes, we will proceed in a similar fashion.

We will also perform an additional per-protocol analysis, which will only include participants whose follow–up examination has taken place at the designated time (6 months after baseline or follow-up ± 2 weeks). Individuals of the intervention group participating in less than 25% of the scheduled walks will be excluded in the per-protocol analysis.

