### Randomisation

Participants will be randomly assigned to either control or experimental group with a 1:1 allocation as per computer-generated randomisation schedule stratified by setting (community [primary care practice, nursing services] or nursing home). Participants will be randomly allocated via a telephone service provided by the Clinical Trial Centre at the University of Marburg (Koordinierungszentrum für klinische Studien [KKS]).

Research assistants will perform the data collection and examinations at baseline (T0) after 6 months of the intervention (T1) and after 12 months of follow up (T2). They will visit each participant either at their home or care home.

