### Blinding

Blinding of participants is not possible due to the type of intervention. For practical reasons, study personnel cannot be blinded either, since at follow-up examinations participants are likely to communicate the study arm they have been allocated to. Moreover, assessments at baseline and follow-up of all participants, management of the intervention and other project tasks will be completed by the same members of the research team. A separation of tasks will not be possible. However, since randomisation will occur only after the baseline examination has been conducted, full concealment of allocation will be assured. In order to keep data collection at follow-up visits as unbiased and consistent as possible, a highly standardised protocol has been developed and will be implemented accordingly.

The study statistician will be blinded to participants’ allocation by being provided only pseudonymised data sets without explicit group allocation (only numbers will be used without revealing which was the intervention or control group).

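### Unblinded staff decide why a visit was missed, and that decision switches the SPPB between 0 and an imputed value; the exposure lies in cause attribution and uncovered reasons

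*Protocol article*

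**What the plan says.** The Missing data section gives the classification to one role: "the research assistant will decide whether an informative (death, admission) or non-informative event" explains the missed assessment. It then links the class to the analysis: "Depending on this categorisation, the following methods for analysis taking into account missing values will be used". The informative class covers participants who could not be examined because of an earlier nursing home admission, a hospital admission or death; they receive an SPPB of 0 under a tied worst-rank method. The non-informative class is described as "not able to attend because participant moved to another place without one of the conditions mentioned above" and is multiply imputed. Reasons are gathered from families, general practitioners or nursing teams.

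On who knows the allocation, the Blinding section says: "For practical reasons, study personnel cannot be blinded either". Baseline and follow-up assessments, "management of the intervention and other project tasks will be completed by the same members of the research team", and "A separation of tasks will not be possible". The one blinded role is downstream: "The study statistician will be blinded to participants’ allocation by being provided only pseudonymised data sets without explicit group allocation".

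**The concern.** The classification replaces an observation of the primary endpoint. One answer gives the lowest possible score; the other gives a value drawn from the imputation model. The person answering knows the arm and belongs to the team that manages the intervention. Blinding the statistician does not protect this step, because the class is already in the data set on arrival.

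If borderline cases were coded differently in the two arms, even without intent, the treatment contrast would shift with no difference in physical function. Unlike unblinded SPPB testing, which the article presents as unavoidable, most of this exposure can be avoided.

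**Working it through.** **1. Where judgement enters.** Setting the Missing data, Blinding, Randomisation and Data analysis sections and Table 1 side by side:

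- *Little judgement:* death and hospital stay. Table 1 collects the date and ICD-10 reason for death, and admission date, discharge date and reason for hospital stays.
- *Judgement on cause:* the rule asks whether the event caused the missed visit, not only whether it happened. An earlier admission counts, but no time window is set. A participant admitted in month 2 who declines in month 6 could go either way. Assistants visit people at home or in the care home, so a nursing home admission need not prevent an assessment, and someone must judge that it did.
- *No assigned class:* refusal, withdrawal, and illness at home without admission. They are neither admission or death nor a move. For withdrawal, the Data analysis section says only that a final evaluation will be requested.

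**2. The plan's own figures.** Inputs from Sample size: SD 2.8, R² 0.5, difference 1 point (standard deviation of the means 0.50), alpha 5%, power 95%, loss 40%.

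- Residual SD = 2.8 × √(1 − 0.5) = 1.98.
- Normal approximation: n per arm = 2 × (1.960 + 1.645)² × 1.98² / 1² ≈ 102. The exact noncentral F gives power 0.9503 at 103 per arm, as stated.
- 206 / 0.6 = 343.3, or 344 in even numbers, against 345 stated. The figures reproduce.

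**3. How many participants pass through the step.** With about 172 per arm, 0.40 × 172 ≈ 69 miss T1 at the planned loss, and 0.28 × 172 ≈ 48 at the pilot study's loss. The document does not say how many would be ambiguous.

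**4. Shift per recoded participant.** Assumption, not in the document: the SPPB otherwise imputed averages 6, range 4 to 8. Shift in the arm mean = imputed mean / 172.

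| Imputed mean | One participant | Nine participants |
|---|---|---|
| 4 | 0.023 | 0.21 |
| 6 | 0.035 | 0.31 |
| 8 | 0.047 | 0.42 |

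**5. False-positive rate, no true effect.** Scenario: 28% of one arm and 23% of the other scored 0, a gap of 0.05 × 172 ≈ 9 people. With imputed mean 6 and SD 2.8:

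- Average zero share 0.255. Outcome variance = 0.745 × 7.84 + 0.255 × 0.745 × 36 = 5.84 + 6.84 = 12.68.
- Explained by baseline = 0.745² × 3.92 = 2.18. Residual SD = √10.50 = 3.24.
- SE of the difference = 3.24 × √(2/172) = 0.349. Shift = 0.05 × 6 = 0.30. Ratio 0.86.
- Rejection = P(Z > 1.96 − 0.86) + P(Z < −1.96 − 0.86) ≈ 14%.

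Simulations of this scenario with 172 per arm, analysed by ANCOVA and by Mann-Whitney, gave 12–15%, against 4–5% with equal zero shares. A gap of about five people gave 8–9%, and about three gave 6%.

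**The case against.** The strongest reply is that this is not open discretion. The article names the informative events, takes reasons from outside informants and collects dates. The Sample size section expects loss to come mainly from death and hospitalisation, so on the plan's own account most missed visits fall in the checkable class. Home visits and the request for a final evaluation at withdrawal reduce the unclear cases. The first sentence of Missing data gives moving only as an example, so the non-informative class may be wider than the later parenthesis suggests. The lack of blinding is openly admitted.

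Much of this stands. A reader might infer that knowledge of allocation can set the primary outcome for any missed visit; the document does not support that, because a dated death or hospital stay is hard to recode. Nor does it show that ambiguous cases will differ between arms, or that nine would be miscoded in one direction. Comparing the shift with a treatment effect diluted to 0.6 point by 40% loss would also be wrong: that figure scores every lost participant 0, which leaves nobody to reclassify. And because the worst-rank analysis uses only ordering, the mean shift is an illustration; the Mann-Whitney simulations speak more directly to that analysis.

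The reply does not settle cause attribution or the unassigned reasons. The standardised protocol in the Blinding section is described for follow-up visits, not for missed ones. A fuller plan might list reason codes, but the article itself already fixes who decides and between which two classes.

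**Conclusion.** The concern holds in a limited form. The article places an arm-aware decision between a missed visit and the primary endpoint value. The exposure is confined to whether an earlier admission caused the missed visit and to refusal, withdrawal and illness without admission.

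The size is a scenario, not an estimate. It rests on an assumed imputed mean of 6 (4 to 8) and on miscoding that runs in one direction. About nine such cases would be material against the 1-point design effect and would more than double the nominal error rate; about three would leave it near nominal. The number of ambiguous cases cannot be derived from the document.

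**What to change.** - The assistant records facts only: a reason from a closed, exhaustive list, its source, and the dates of death, admission and discharge.
- A rule fixed before unblinding maps each code to worst rank or imputation. It includes a time window linking an admission to the missed visit. The already blinded statistician applies it.
- Refusal, withdrawal and illness without admission are assigned in advance. Health-related reasons should follow the plan's own rationale for informative missingness; sending illness at home to imputation by default would treat it as non-informative.
- Counts per code are reported by arm, and a sensitivity analysis codes the ambiguous cases both ways.

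The cost is about one form field and a little more analysis, since reasons and event dates are already to be collected. Some judgement remains, because an unblinded assistant still records the reason; the route for bias is narrowed, not closed.

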### Aims

Our research questions are:
Compared to controls, does volunteer-supported walking improve physical function and quality of life as well as lower fear of falling? Furthermore, improves supported walking the cognitive executive function and the general physical activity? [Effectiveness]Compared to controls, does volunteer-support walking increase the rate of falls needing medical attention, rate of admissions to hospital, duration of hospitalisations and mortality? [Safety]Compared to controls, does supported walking have an impact on the frequency and duration of hospitalisations and/or mortality? [effectiveness, safety]

Finally, we explore whether the intervention can be successfully implemented into existing community services.

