#### Falls questionnaire (T1, T2)

This questionnaire, answered by the participant, serves to find out whether she/he experienced any falls during the intervention. The participant states whether falls required medical attention, what kind of treatment was needed and by whom it was provided.

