### Outcomes

We expect the intervention to impact upon muscle strength, balance and ability to walk. We therefore chose the Short Physical Performance Battery as the main outcome of the study. SPPB scores have been shown to be associated with disability in mobility and activities of daily living [26–28], future hospitalisation [29], health improvement [30] and mortality [30–32]. For these simple measures of performance, the SPPB shows a good reliability and validity [27].

As secondary outcomes we will evaluate quality of life (EQ-5D-5L), fear of falling (FES-I), physical activity (activity diary), cognitive executive function (clock drawing test), falls requiring medical attention, hospitalisation and death.

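### The worst-score rule for missed visits is extended to every secondary outcome, including treated falls, hospitalisation and death, and so distorts the safety comparison

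*Protocol article*

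**What the plan says.** The Missing data section of the protocol article sorts missed T1 or T2 evaluations by cause.

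- **Informative** (nursing home admission, hospital admission or death): "tied worst rank score method will be assigned a SPPB Score = 0", followed by a worst-rank analysis.
- **Non-informative** (the participant moved away and none of those conditions applies): "we will proceed with multiple imputation".

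The sentence "For secondary outcomes, we will proceed in a similar fashion" appears three times, under both branches, and exempts no outcome.

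The Outcomes section ends its list of secondary outcomes with "cognitive executive function (clock drawing test), falls requiring medical attention, hospitalisation and death". The Aims section makes the same events the safety question, asking first "does volunteer-support walking increase the rate of falls needing medical attention". For the event outcomes, Data analysis says "we will either calculate a χ2-test, Fisher exact test for binary variables or conduct a log-rank-test". It also defines the intention-to-treat set as everyone randomised.

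Treated falls have two sources under Measurements. One is a questionnaire answered by the participant: "The participant states whether falls required medical attention, what kind of treatment was needed and by whom it was provided". The other is a separate form on which medical staff give the date and diagnosis. For a missed visit, the Missing data section says: "Information on reasons for missing the T1 or T2 evaluation will be obtained from participants’ families, general practitioners or nursing teams".

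**The concern.** A worst score makes sense for a scale such as the SPPB, where death or institutionalisation can reasonably rank below any measured value. It does not carry over to a yes/no safety event. There the worst value is that the event happened, and the rule is triggered by a missed examination, not by missing event data. Someone absent because of a nursing home admission would take the worst value on treated falls, hospitalisation and death, although the admission is none of these. Someone in hospital with pneumonia at T1 would count as a faller, and on the same logic as dead.

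The number affected is not small. The sample size section plans for 40% loss by T1 and attributes it mainly to death and hospitalisation, which fall in the informative class. Treated falls are the most natural harm of a walking programme in frail people, so the comparison at risk is the one a safety reader will look at first.

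**Working it through.** **The plan's own figure.** The residual SD is 2.8 × √(1 − 0.5) = 1.98. With a difference of 1 point, two-sided 5% and 95% power, the normal approximation gives 102 per arm. The F test gives power 0.9503 at 103 per arm, so the stated 103 reproduces. Allowing for 40% loss, 206 / 0.6 = 343.3, or 344, against the stated 345. With 1:1 allocation that is about 172 per arm. The documents give no rate or power for falls, hospitalisation or death.

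**Inputs for the illustration**
- 172 per arm (345 / 2, rounded down).
- Informative share m in each arm: 20% (half the planned loss), 28% (total pilot loss) and 40% (total planned loss). The last two are upper bounds for their sources, because not all loss is informative.
- True treated-fall risk of 10% in controls and 20% with walking. This is an assumption.

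**Effect of the rule.** If everyone informatively missing is recorded as a faller, a true risk p becomes m + (1 − m)p, and the risk difference shrinks by the factor (1 − m). For example, at m = 0.20 the control risk is 0.20 + 0.80 × 0.10 = 0.28 and the walking risk is 0.20 + 0.80 × 0.20 = 0.36.

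Power is Φ(|difference| / SE − 1.96), with SE = √{[p₁(1 − p₁) + p₂(1 − p₂)] / 172}. With true status known for all, SE = √(0.25 / 172) = 0.0381, and power = Φ(2.62 − 1.96) = 75% (74% with a pooled variance under the null).

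| Informative loss, both arms | Control | Walking | Risk ratio | Power |
|---|---|---|---|---|
| None (true status known) | 10% | 20% | 2.00 | 75% |
| 20% | 28.0% | 36.0% | 1.29 | 36% |
| 28% | 35.2% | 42.4% | 1.20 | 28% |
| 40% | 46.0% | 52.0% | 1.13 | 20% |

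**Other assumed risks.** Going from full ascertainment to the rule at m = 40%, power falls from 65% to 12% for 5% against 12%, and from 92% to 39% for 15% against 30%.

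**Unequal loss**
- True risks 10% and 20%, informative loss 40% in controls and 28% with walking: 46.0% against 42.4%. The sign reverses.
- Same risks, loss 28% and 40%: 35.2% against 52.0%. The true 10-point rise becomes 16.8 points.
- No true effect (10% in both arms), loss 28% and 40%: 35.2% against 46.0%. A false rise of 10.8 points appears.

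**The case against.** The strongest reply is that the rule was never meant for events. Data analysis assigns ANCOVA, t-tests and Mann-Whitney tests to the secondary outcomes, and gives deaths, treated falls and hospital treatments their own sentence with other tests. A worst-rank score has no clear counterpart in a log-rank test, where censoring is usual, and no sentence says outright that falls are filled in as events. That stands as evidence of intent. It does not remove the conflict: the Outcomes section calls these events secondary outcomes, the extension exempts none, and separate tests are not a separate missing-data rule. A χ² or Fisher test on all randomised participants needs a value for each person not seen, and the only model offered is the worst value.

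Second, treated falls are also reported by medical staff, so a missed visit need not mean missing fall data. This is correct, and a reader who infers from the participant questionnaire alone that the falls of absent people are lost goes too far. But no section says that the staff form is completed when T1 or T2 is missed, or that it takes precedence over an assigned value. For missed visits the article mentions obtaining reasons. It does not exclude asking for more.

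Third, a reader might infer that those who moved away would have deaths or admissions invented for them. The text does not support this. The imputation class excludes anyone absent because of death or admission, and multiple imputation does not by itself turn non-events into harms.

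Fourth, many informatively missing people truly died or were hospitalised, and their fall risk may be higher than that of people seen. Both points reduce the number of false events. The false entries are clearest for falls and for admitted survivors counted as dead. A higher risk among the missing does not rescue the rule: with assumed risks of 30% and 50% among the missing and m = 28%, the true figures are 15.6% and 28.4% (risk ratio 1.82), and the rule still returns 35.2% and 42.4% (1.20).

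Finally, full ascertainment is a demanding comparator. Simply leaving the missing out gives about 60% power at 28% loss and 53% at 40%, which is still well above 28% and 20%.

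**Conclusion.** The point holds as a matter of scope. The article states a missing-data rule and extends it to all secondary outcomes, and that set includes the trial's safety events. This is a stated rule that reaches too far, not a detail left to the analysis plan.

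It is tempting to conclude that a rise in falls would be masked. The documents do not support so firm a claim. Dilution follows when informative loss is similar in the two arms; when it differs, the rule can exaggerate, reverse or create a difference. How the rule would be applied to a yes/no event is also left undefined, so the figures describe its literal reading.

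On that reading, a risk ratio of 2.0 shrinks to 1.29 at 20% informative loss and to 1.13 at the 40% bound, with power falling from about 75% to 36% and 20%. These sizes rest on assumed fall risks, equal informative loss and, in the table, the same fall risk in missing and seen participants. The direction of the dilution under equal loss does not depend on the particular rates assumed. The matter should be corrected before analysis.

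**What to change.** 1. State in the Missing data section that the worst-score and multiple-imputation rules apply, beyond the SPPB, to scale outcomes only (EQ-5D-5L, FES-I, clock drawing), and not to treated falls, hospitalisation or death.
2. For every randomised participant, including those not seen at T1 or T2, complete the treated-falls, hospitalisation and death data from the medical-staff form and from the contact with general practitioners and nursing teams that is already planned for missed visits. Cover the time from randomisation to death, last known contact or 12 months.
3. Analyse ascertained events. Censor at last known contact, and treat death as a competing event for falls and hospitalisation. Censoring alone is not enough in a population where death is an expected cause of loss.

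The cost is one or two sentences in the plan, a few more questions in an existing contact, and consent wording that covers information from care providers after a participant stops attending.
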